### 7.3.3 Patient questionnaires

To assess patients wellbeing and satisfaction, all included patients will receive digital validated questionnaires on the first day of inclusion, before discharge and at 4 weeks after delivery in Research Manager® on their tablet or smartphone. All surveys are attached as appendix (A, B and C). For further description and analysis of the questionnaires see sections 7.1.2 and 9.2.1.

### 7.3.4 Follow-up

All patients will be followed up for six weeks to obtain neonatal and maternal outcomes. Data on maternal and neonatal mortality and morbidity will be noted during the routine postpartum check-up in the hospital or by their primary care midwife. Missing data will be requested from their primary care midwife, the child health clinic, the general physician, the pediatrician, and/or the gynecologist.

### **7.3.5 Data collection**

At study entry, baseline data such as patient demographics, medical and obstetric history and current pregnancy details are collected. Relevant clinical data of mother and child during admission (e.g. gestational age, birth weight, Apgar scores, umbilical cord blood gas analysis) and until six weeks postpartum will be collected. Study parameters will be retrieved from the electronic patient record and questionnaires. Participants will give informed consent for the recruitment of their data until six weeks postpartum. The partner/legal representative who also has parental authority over the neonate will also be asked informed consent for the collection and the use of data of the neonate.

### **7.3.6 Healthcare professionals questionnaire**

All HCPs involved in the HASTA study will receive a digital questionnaire – through mail by Research Manager® – once the last participants has delivered or has reached the GA of 37 weeks. Survey is based on a validated patient questionnaire (31) and suitable for HCPs after minimal adjustments. The validated survey is attached to appendix B. For further description and analysis of the questionnaires see section 9.2.1.

## **7.4 Withdrawal of individual subjects**

Subjects can leave the study at any time for any reason if they wish to do so without any consequences. The investigators and HCPs can decide to withdraw or exclude a subject from the study when subject did not meet inclusion and exclusion criteria, when intervention was not received or for urgent medical reasons making measurements impossible or unsafe.

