#### **4.4 Sample size calculation**

In a previous cohort study for conventional remote CTG monitoring, 4% of all tracings needed repetition (562 out of 12,649) and 0.9% (N=111) of the CTGs had to be repeated in the hospital. The success rate at first trace was 95.5% and after repetition 99% (28) .

A success rate of 90% is considered clinically sufficient based on previous studies (28-30) and HCPs' opinion. Only the first day of remote eCTG measurements will be used for determination of the feasibility by assessing the signal quality and success. If the remote eCTG measurement is technically insufficient but reassuring – according to current clinical policy – it can be repeated once at the same day and still be considered successful. Calculated on 90% chance of success according Wilson standard error of proportions (CI95% > lower limit of 82.5%), 60 subjects are needed for inclusion in this cohort study.

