## **7.5 Replacement of individual subjects after withdrawal**

When a subject withdraws from this study or does not meet the inclusion criteria – before start of the study interventions – no study number will be created and we will approach another patient for participation so that the requested sample size will be reached. An overview of inclusions, exclusions, refusals and missed eligible patients will be maintained in an “enrollment log” on the local server at the MMC, which will be protected by a password and has limited access by the healthcare providers directly involved.

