## **7.6 Follow-up of subjects withdrawn from treatment**

After withdrawal, there will be no follow-up of subjects.

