## 9. STATISTICAL ANALYSIS

### 9.1 Primary study parameter(s)

Primary data statistical analyses will be performed using SPSS version 29 (IBM Corp., Armonk, NY, USA) and SAS software version 9.4 (SAS Institute Inc., Cary, NC, USA). Signal quality will be defined as the percentage of time (minutes) in which the remote eCTG device delivers an FHR value. Signal quality will be determined for each patient. Mean, SD, and 95% confidence interval (CI) of the mean success rate will be calculated using a one-sample t-test. The one-way ANOVA analog, Kruskal-Wallis test will be used in when no normal division of outcomes is found. Success rate will be defined as the number and percentage (N/%) of remote eCTG registration the first day of inclusion with at least 30 minutes interpretable signal quality and/or less than 20% signal loss during 30 to 90 minutes measurement (see section 7.1.1).

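### Women withdrawn by staff lose the promised six-week follow-up, and an included woman with no first-day recording can leave the primary denominator

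*Protocol*

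**What the plan says.** Protocol section 7.4 allows investigators and healthcare professionals to withdraw or exclude a subject "when subject did not meet inclusion and exclusion criteria, when intervention was not received or for urgent medical reasons making measurements impossible or unsafe". Section 7.6, which by its heading concerns women withdrawn from treatment, states "After withdrawal, there will be no follow-up of subjects".

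Section 7.3.4 states "All patients will be followed up for six weeks to obtain neonatal and maternal outcomes". Section 7.3.5 adds that participants consent to the use of their data until six weeks postpartum, and that study parameters are retrieved from the electronic patient record and questionnaires.

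For the primary outcome, section 9.1 states "Success rate will be defined as the number and percentage (N/%) of remote eCTG registration the first day of inclusion" and adds the signal criteria. Section 7.3.2 says that an eCTG still not interpretable after repetition on the first day is not successful. Section 7.5 covers women who withdraw or prove ineligible before the interventions start: "no study number will be created and we will approach another patient for participation so that the requested sample size will be reached". Exclusions and refusals go into an enrollment log. Section 4.4 gives the yardstick: "A success rate of 90% is considered clinically sufficient".

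**The concern.** There are two problems.

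The first is lost outcome data. Maternal and perinatal outcomes are secondary parameters (section 7.1.2). A woman taken out for an urgent medical reason is more likely than others to have an adverse outcome, yet section 7.6 stops her follow-up. The overlap is visible in the text. HELLP, signs of placental abruption and signs of chorioamnionitis are exclusion criteria in section 4.3, and the same three conditions are maternal morbidity outcomes in section 7.1.2. Section 7.3.2 continues the interventions for outpatients who are later hospitalized only while they still meet the inclusion and exclusion criteria. A woman who deteriorates could therefore be withdrawn just as her outcome becomes relevant, and the morbidity tables would then be too favourable.

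The second is the primary denominator. The study asks whether women can obtain a usable tracing by themselves. If an included woman was given the kit and no recording resulted, that answers the question in the negative. Section 7.4 makes non-receipt of the intervention a ground for exclusion without defining it, and section 9.1 counts registrations, not women. She can therefore be absent from both numerator and denominator, and the success rate rises.

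**Working it through.** **Follow-up: the sections side by side.**

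- Section 7.3.4: all patients, six weeks, no exception.
- Section 7.3.5: consent covers data until six weeks postpartum, with outcomes taken from the record.
- Section 7.6: no follow-up after withdrawal, whoever decided on it and for whatever reason.
- Section 8.2.2: serious adverse events are reported from application until twelve hours after device removal, and events due to the pregnancy or its disease are exempt. Safety reporting therefore does not recover the later outcomes.

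Sections 7.3.4 and 7.6 cannot both be followed for a woman withdrawn by staff whose consent still stands. With 60 women, one event is 1/60 = 1.7%. Suppose, as an assumption, that three women have a given outcome and two of them are withdrawn and not followed. The true figure is 3/60 = 5.0% and the reported figure is 1/58 = 1.7%.

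**Primary rate: the plan's own figure.** Section 4.4 states "Calculated on 90% chance of success according Wilson standard error of proportions (CI95% > lower limit of 82.5%), 60 subjects are needed". With p = 0.90 and z = 1.96:

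- Wald lower limit, p − z√(p(1−p)/n): 0.90 − 1.96 × √(0.09/60) = 0.90 − 0.076 = 82.4%. The smallest n reaching 82.5% is 62, so 60 is reproduced to within two women.
- Wilson lower limit, [p + z²/2n − z√(p(1−p)/n + z²/4n²)] / (1 + z²/n), at n = 60: (0.9320 − 0.0824)/1.0640 = 79.9%.

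The 60 therefore fits Wald and not the Wilson method named. That is a separate matter. Wilson is used below because the protocol names it.

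**Effect of dropping failures.** The protocol gives no number of exclusions, so a range is assumed. If k failures without a recording leave the denominator, s/60 becomes s/(60 − k). Two-sided 95% Wilson lower limits are in brackets.

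| All 60 kept | k dropped | Rate reported |
|---|---|---|
| 54/60 = 90.0% (79.9%) | 2 | 54/58 = 93.1% (83.6%) |
| 54/60 = 90.0% (79.9%) | 3 | 54/57 = 94.7% (85.6%) |
| 53/60 = 88.3% (77.8%) | 2 | 53/58 = 91.4% (81.4%) |
| 52/60 = 86.7% (75.8%) | 3 | 52/57 = 91.2% (81.1%) |
| 51/60 = 85.0% (73.9%) | 4 | 51/56 = 91.1% (80.7%) |
| 50/60 = 83.3% (72.0%) | 5 | 50/55 = 90.9% (80.4%) |

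For 54/58 the Wilson step is (0.9642 − 0.0731)/1.0662 = 83.6%. At 53/60, dropping two failures carries the point estimate past the 90% called clinically sufficient. Dropping one does not (53/59 = 89.8%).

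**The case against.** The strongest reply is that the main way of failing is already counted. Section 7.3.2 classes a tracing that is uninterpretable after repetition as not successful, and section 7.1.2 counts repeats, switches for poor signal and premature closures. This stands. A reader might infer from section 7.4 that any technically impossible measurement can be excluded. The text does not say so: it ties impossibility to urgent medical reasons, and signal failure is not a listed ground. The gap is confined to women with no recording at all. It is made less likely because staff go through all the steps with the woman before her first measurement.

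A reader might also take the replacement rule in section 7.5 as a way of discarding failures. It applies only before the interventions start and those women are logged, which is ordinary practice. Nor does crossing 82.5% reverse a decision: section 4.4 uses that figure to size the study, and the protocol states no pass/fail rule. The examples remove failures only, so they show sensitivity and not an expected bias.

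On safety, a switch to conventional CTG or a clinical deterioration is not itself called withdrawal, unscheduled visits and re-admissions are recorded, and adverse events are followed until they resolve or stabilise (section 8.2.3). Section 7.6 might also be read as a specific exception to section 7.3.4. All this narrows the loss to women formally withdrawn, but does not remove it. Under the exception reading their outcomes still go uncollected although consent stands. An analysis plan not seen here could define the denominator. It could not restore outcomes that were never collected.

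**Conclusion.** The point stands in two parts of unequal strength. The conflict between section 7.6 and sections 7.3.4 and 7.3.5 is in the text. Followed as written, it causes informative loss of maternal and perinatal outcomes among women formally withdrawn.

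The denominator part is a narrower risk. It concerns included women with no first-day recording and rests on section 9.1 counting registrations and on section 7.4 leaving non-receipt undefined. Its size is unknown because no number of exclusions is given. If two failures were lost this way, the reported rate would rise by about 3 percentage points (90.0% to 93.1%, or 88.3% to 91.4%). The documents do not show that the primary rate will be biased upward, only that the wording allows it and that a few women are enough to matter.

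**What to change.** (a) Reconcile section 7.6 with sections 7.3.4 and 7.3.5. State that stopping eCTG, or being withdrawn by the investigator or healthcare professional, does not end data collection. Maternal and neonatal outcomes continue to be taken from the patient record to six weeks postpartum unless the woman withdraws consent for data use.

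(b) In sections 7.4 and 9.1, keep every consenting woman handed the kit in the primary denominator. Count the absence of a usable first-day recording for device, user or logistic reasons as not successful. Report women with no recording for urgent medical reasons separately, with a sensitivity analysis that counts them as not successful.

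(c) Keep the section 7.5 replacement for women lost before the kit is handed over, and list them from the enrollment log.

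The cost is protocol wording. Outcomes are already retrieved from the record, and clinical freedom to stop or switch monitoring is untouched. The downside is that the reported success rate may be slightly lower.

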## **7.5 Replacement of individual subjects after withdrawal**

When a subject withdraws from this study or does not meet the inclusion criteria – before start of the study interventions – no study number will be created and we will approach another patient for participation so that the requested sample size will be reached. An overview of inclusions, exclusions, refusals and missed eligible patients will be maintained in an “enrollment log” on the local server at the MMC, which will be protected by a password and has limited access by the healthcare providers directly involved.

## **7.6 Follow-up of subjects withdrawn from treatment**

After withdrawal, there will be no follow-up of subjects.

## **7.7 Premature termination of the study**

Not applicable.

## **8. SAFETY REPORTING**

### **8.1 Temporary halt for reasons of subject safety**

In accordance to section 10, subsection 4, of the WMO, the sponsor will suspend the study if there is sufficient ground that continuation of the study will jeopardise subject health or safety. The sponsor will notify the accredited METC without undue delay of a temporary halt including the reason for such an action. The study will be suspended pending a further positive decision by the accredited METC. The investigator will take care that all subjects are kept informed.

### **8.2 AEs, SAEs and SUSARs**

#### **8.2.1 Adverse events (AEs)**

Adverse events are defined as any undesirable experience occurring to a subject during the study, whether or not considered related to the investigational product (e.g. skin irritation or minor (local) allergic reaction occurring within twelve hours after removal of the investigational product). All adverse events reported spontaneously by the subject or observed by the investigator or his staff will be recorded.

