**Nature and extent of the burden and risks associated with participation, benefit and group**

**relatedness:** Participation in this study is expected not to cause any risk for the patient or fetus. In case eCTG registration is insufficient, a switch to the conventional CTG can be made.

The benefits of eCTG monitoring with Nemo Remote® include the fact that it is wireless, non-invasive and well positionable without the help of elastic belts. As a result, repetitive repositioning to reduce signal loss - as required when using conventional CTG frequently performed with the support of healthcare professionals (HCPs) - is not needed. This is beneficial for future implementation of home monitoring throughout pregnancy, thereby increasing the patient's autonomy. Conducting self-administered remote eCTG home monitoring in a hospital setting, enables the evaluation of the feasibility at home - most likely - without any risk to patient or fetus. Patients using Nemo Remote® have a very small – known and unrelated to remote monitoring – probability of developing skin irritation or a minor (local) allergic reaction to the skin electrodes from the abdominal patch. There is no need for treatment if skin irritation happens, as this will naturally resolve over the course of days once the patch is removed (as in NIEM-O W22.070, NIEM-II W22.071). Measurements of the umbilical- and uterine artery are widely applied in routine obstetric care and are known not to cause any harm to patient and/or fetus (3). At three moments participants will be asked to fill in digital questionnaires. All other interventions are standard care. No additional – study-related – hospital visits or fetal registrations are needed.

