### 5.1 Investigational treatment

All patients will receive routine care following national guidelines and/or local protocols. Participants at the clinic will receive self-administered remote eCTG monitoring by NRM once a day (*Figure 1*). In case of follow-up at the outpatient clinic, participants will receive self-administered remote eCTG monitoring by NRM once per day or at least twice a week, depending on their care path. The realtime eCTG measurement will be instantly transferred digitally to the hospital electronic patient file (Chipsoft HiX) and assessed real-time on interpretability by the HCP. Monitoring will last between 30-90 minutes depending on the interpretability and reassurance of the remote eCTG measurement. Criteria defining a successful measurement are described in a standard operating procedure (SOP) and will be available for HCPs at the hospital to avoid prematurely closing of the eCTG measurement (see section 7.1.1). All HCPs involved in this study will receive training on the study protocol. The study procedure and statistical analysis are described in section 7.3.2, chapter 9 and in *Figure 12*.

Monitoring will be repeated the same day when reassuring but insufficiently interpretable, or upon request of the HCP in case of concerns about maternal and/or fetal condition. Additional detailed information of the NRM is described under investigational product (chapter 6). When remote eCTG interpretability is insufficient – based on clinical assessment of HCPs – a switch to conventional CTG monitoring will take place. In this study, HCPs will be asked to define clearly if a switch to conventional CTG was made based on insufficient interpretability or because of concerns about fetal and/or maternal condition (section 7.1.2).

From the second day onward, synchronized US Doppler measurements (clips of 2 x 5 minutes) of the umbilical and uterine arteries will be performed simultaneously with the remote eCTG for 24 patients ([images removed]

*Figure 3*). Measurements of two groups - cardiovascular low (PPROM; N=12) versus cardiovascular high-risk (PE/FGR; N=12) - will be collected and analyzed to evaluate the feasibility of synchronized multimodal acquisitions of maternal and fetal measurements.

[images removed]

*Figure 3. Measurement fetal and maternal heartrate, Doppler arteria umbilicalis, Doppler uterine artery and uterine activity.*

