#### 7.1.2 Secondary study parameters

##### *Remote eCTG parameters*

- Number of days with remote monitoring per participant.
- Number of remote eCTG measurements per participant.
- Need to repeat remote measurements the same day because of reassuring but insufficient interpretability.
- Number of switch to conventional CTG and possible maternal and/or fetal reason.
- Number of switch to conventional CTG needed because of poor signal of remote eCTG measurement and possible cause.
- Success rate of CTG measurement after switch based on same criteria as in remote eCTG monitoring (7.1.1).
- Incidence of skin irritation.
- Number of “unscheduled visits” and reason.
  - When there is an indication for an additional visit in-hospital as if the participant is monitored at home (e.g. contractions, decreased fetal movements, PE symptoms, suspicion of PPRM).
- Number of “re-admissions” and reason.
  - When there is an indication of admission as if the participant is monitored at home (e.g. blood loss, threatened premature labor, hypertension with indication for intravenous medication).
- The number of eCTG measurements assessed successful at closure by HCP.
- The number of eCTG measurements prematurely closed by HCP before complying the criteria of a successful measurement (7.1.1).

- Maternal and fetal factors HCPs have included in their assessment of the eCTG measurement (e.g. GA, fetal growth, Doppler measurements, PPRM).

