- Once the eCTG measurement is considered successful – or when the maximum of 90 minutes has exceeded – the HCP will send a message in the Luscii app® and will contact the participant by telephone a few minutes later, the time they have stopped the remote eCTG measurement. All findings will be discussed with the participant and completed in the patients' file in HiX. In addition, the HCP will visit the participant in the hospital room.
- When eCTG measurement is not successful but reassuring, the measurement will be repeated the same day on a moment agreed between participant and HCP (PA).
- When eCTG measurement is not interpretable after repetition on the first day of inclusion, eCTG will be defined not successful – primary outcome – and a switch to conventional CTG will take place. Equally to routine care, in- hospital care is needed and home- monitoring will not be possible.
- When after an additional clinical visit by the HCP (PA) “unscheduled consult” at participants room for other reasons than signal quality concerns (e.g. contractions, reduced fetal movements, patients concerns), without indication for hospitalization – eCTG adequate and reassuring – participants can continue “home monitoring” through eCTG like it will be once home monitoring is implemented in the future. No switch to conventional CTG will be needed. This additional visit will be recorded as part of the patient journey for later cost analysis purposes (*Figure 11, Table 2*).
- As long as remote eCTG measurements are successful, participants will continue the study interventions until discharge, delivery or when 37 weeks is reached. At any moment – when demanded by the participants or by the HCP – a switch to conventional CTG will be made.
- When reached a GA of 37 weeks, after delivery or at discharge, participants will be asked to fill in a second digital questionnaire (5.1, 7.3.3), and at 4 weeks after delivery a third questionnaire.

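### Skin irritation is a secondary outcome and the device harm the protocol names, but the only written rule for finding it is passive, so the reported incidence is likely to be a lower bound

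*Protocol*

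**What the plan says.** Skin irritation has two roles in the protocol.

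- It is the expected device harm. The Summary gives participants a very small "probability of developing skin irritation or a minor (local) allergic reaction to the skin electrodes from the abdominal patch", and sections 6.4.4 and 10.4 return to the same harm. No rate is given.
- It is an outcome. Section 7.1.2, under the remote eCTG parameters, lists "Incidence of skin irritation", with no definition, assessor or time point.

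On how it is found, 8.2.1 offers as its example of an adverse event "skin irritation or minor (local) allergic reaction occurring within twelve hours after removal of the investigational product" and then states: "All adverse events reported spontaneously by the subject or observed by the investigator or his staff will be recorded". Section 7.3.5 takes study parameters from the electronic patient record and the questionnaires.

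The use of the patch and the contact after a recording depend on setting. Section 5.1 says of admitted women: "Participants at the clinic will receive self-administered remote eCTG monitoring by NRM once a day". Women followed as outpatients are monitored "by NRM once per day or at least twice a week, depending on their care path". In 7.3.2 both groups receive a message and a telephone call after the recording. For hospitalized participants the text adds: "In addition, the HCP will visit the participant in the hospital room". The parallel outpatient item has no such sentence.

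**The concern.** An incidence is only as good as the effort to find the events. Mild skin redness that clears by itself is the kind of event a woman may not volunteer, particularly when her attention and that of the staff is on the fetus. If nobody asks, the count depends on who happens to mention it or look.

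The study is meant to prepare for self-applied monitoring at home, and section 12.1 says this device has not been used in previous research. The protocol calls the risk very small without a figure, so this study is where a figure would come from. If it is too low, it will wrongly appear to confirm that statement. Denominators and subgroup splits can be settled at the analysis stage. Missing event reports cannot.

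**Working it through.** There is no stated figure to reproduce: the protocol gives no skin-irritation rate, detection probability, ward/clinic split or target precision. The main check is therefore of the text.

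**Step 1. Is there any written route that asks about the skin?**

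- Adverse events (8.2.1): spontaneous report or staff observation. Not solicited.
- Luscii entry (5.1 and 7.3.2): the symptoms named are pre-eclampsia symptoms, abdominal pain, contractions, blood loss and fetal movements. The skin is not named, though the list is given as examples.
- EQ-5D-5L (Appendix A): no skin item.
- D-QUEST (Appendix B): items on safety and comfort of the device, with space for a reason for dissatisfaction. No skin item.
- CSQ-8 (Appendix C): no skin item.
- Patient record (7.3.5): holds a skin finding only if someone noted one.

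No solicited skin question is written anywhere.

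**Step 2. Do the two settings have the same chance of detection?**

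- After the recording, both settings have the message and telephone call, in which the findings are discussed. Only the ward text adds a room visit.
- The example in 8.2.1 covers a "minor (local) allergic reaction occurring within twelve hours after removal of the investigational product". An outpatient may have left by then, although the text does not say when she leaves.

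A difference in detection is plausible but not stated.

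**Step 3. Is the exposure the same?**

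Taking one patch per measurement, a ward participant has about 7 a week and a clinic participant 2 to 7. The ratio runs from 7/2 = 3.5 at the clinic minimum down to 1 if the clinic participant measures daily.

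**Step 4. Illustration under assumed risks.**

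Let q be an assumed risk per application and k the number of applications. If applications are independent, incidence per woman = 1 − (1 − q)^k. For one week, with k = 7 on the ward and k = 2 at the clinic minimum:

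| q (assumed) | Ward | Clinic | Ratio |
|---|---|---|---|
| 1% | 6.8% | 2.0% | 3.4 |
| 2% | 13.2% | 4.0% | 3.3 |
| 5% | 30.2% | 9.8% | 3.1 |

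At q = 2% the pooled incidence depends on the share on the ward:

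- 25% ward: 0.25 × 13.2% + 0.75 × 4.0% = 6.3%
- 75% ward: 0.75 × 13.2% + 0.25 × 4.0% = 10.9%

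Now add incomplete detection, assumed at 90% on the ward and 50% at the clinic, with half the women in each setting and q = 2%:

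- true: 0.5 × 13.2% + 0.5 × 4.0% = 8.6%
- observed: 0.5 × 0.90 × 13.2% + 0.5 × 0.50 × 4.0% = 6.9%

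With the same detection and mix, q = 1% gives 4.4% true and 3.6% observed; q = 5% gives 20.0% and 16.0%.

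**Step 5. Precision.**

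Wilson 95% intervals at N = 60: 0/60 gives 0 to 6.0%, 3/60 gives 1.7% to 13.7%, 6/60 gives 4.7% to 20.1%.

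**The case against.** A reader might go further and infer that the pooled incidence cannot be interpreted at all. The documents do not support that. Section 7.1.2 collects the number of remote measurements and of monitoring days per participant, and its cost sub-analysis separates women by setting at inclusion. A rate per measurement and a split by setting therefore need no new exposure data, and the choice of denominator may properly be left to an analysis plan that is not shown.

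Other parts of the opposing case also stand:

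- The ward/clinic detection gap is inferred from one missing sentence. The room visit is not described as a skin inspection, both settings have the telephone call, and nothing says clinic women leave unseen.
- The twelve hours limits when the reaction occurs, not when it may be reported. The Summary says irritation resolves over days, so it could still be seen or recalled at a later visit.
- The Luscii list is open-ended, the case report form is not shown, and D-QUEST gives a free-text route for complaints.
- A mixture of daily and twice-weekly use is not in itself a bias: the cost section of 7.1.2 treats both as home-monitoring scenarios.
- Every percentage above rests on assumed inputs. If susceptibility varies between women, the independence formula overstates incidence at high patch counts.

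What the objection does not remove is the central gap. For a named outcome the written rule is passive, an open list of examples is not an instruction to ask, and counting measurements does not bring back missed events.

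**Conclusion.** The point holds in a limited form. As written, the incidence of skin irritation is ascertained passively and is likely to be a lower bound. This assumes that some mild reactions are neither volunteered nor noticed, that few reports are false, and that the case report form or app does not already contain a skin item.

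The size is unknown. In the illustration above, a true 8.6% is read as 6.9%, and with other detection probabilities the gap could be larger or smaller. Differential detection by setting is possible but not shown. The dependence of the crude figure on the ward/clinic mix is real when clinic women measure less than daily, and is correctable from data already collected.

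The outcome is descriptive, in 60 women, for a harm described as resolving without treatment. The primary outcome is untouched and no decision rule depends on this figure. Even complete ascertainment would leave a wide interval. The reason to act is that the remedy is cheap and has to be in place before data collection.

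**What to change.** - In 7.3.2 and 8.2.1, add one fixed question about the skin at the previous patch site, worded and asked identically for ward and clinic participants, at every Luscii entry or in the telephone contact after each recording.
- Add the same question to the second questionnaire, to cover the last patch.
- In 7.1.2, state what answer counts as skin irritation and the period it refers to.
- Report the incidence per woman. Also report it per measurement, allowing for repeated measurements within a woman, and by setting, using the measurement counts already planned.
- If data collection has already begun without such a question, describe the figure as spontaneously reported or observed irritation and present it as a lower bound.

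The cost is one extra item in contacts that already take place, and probably a higher reported incidence. No visit, recording or sample-size change is needed.
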